## Abstract

**Introduction::**

Coronary computed tomography angiography (CCTA) has emerged as a valuable noninvasive imaging tool for assessing atheromatous plaque morphology and composition, and several CCTA features have been validated as reliable indicators of the plaque-associated risk. However, the role of lesion geometry as a CCTA feature of plaque vulnerability has not been investigated so far.

**Material and methods::**

Here we present the study protocol of the GEOMETRY trial, a prospective, single center, cohort study in which we aim to investigate the relationship between plaque geometry (as expressed by cross-sectional and longitudinal plaque eccentricity) and the risk for major adverse cardiac events (MACE) during 2 years of follow-up, in order to validate plaque eccentricity as a new CCTA marker of coronary plaque vulnerability. One thousand patients with suspected coronary artery disease (CAD) and pretest probability of CAD between 15% and 85%, who undergo CCTA and in whom CCTA identifies the presence of at least 1 significant coronary plaque (producing a luminal narrowing of at least 50%) will be enrolled in the study. Based on the results of complex image post-processing and plaque analysis, patients will be divided into 2 groups: group 1—patients in whom CCTA analysis identifies only non-eccentric coronary plaque; and group 2—patients in whom CCTA analysis reveals the presence of at least 1 eccentric significant coronary plaque producing a significant luminal narrowing. Study outcomes will consist in the rate of major cardiovascular events and the rate of plaque progression during follow-up.

The study is funded by the Romanian Ministry of European Funds, the Romanian Government and the European Union, as part of the research grant number 103544/2016 – PlaqueIMAGE (contract number 26/01.09.2016).

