### Study objectives

1.2

The primary objective of the study is to evaluate the association between different patterns of plaque geometry and the risk for major adverse cardiac events MACE (defined as all-cause mortality, cardiovascular death, myocardial infarction, repeated revascularization, repeated hospitalizations for cardiovascular related incidents, cerebrovascular events) during a 2-year follow-up.

The secondary objective of the study is to evaluate the association of plaque eccentricity with plaque vulnerability and plaque progression after 2 years of follow-up.

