### Study population

2.3

GEOMETRY will be a non-randomized, observational, single-center study including patients with chest pain and pre-test probability of coronary artery disease between 15% and 85%, referred for CCTA (according to the recommendation of the guidelines of the European Society of Cardiology).^[10]^

Inclusion criteria:

Patients with suspected coronary artery disease (CAD) and pre-test probability of CAD between 15% and 85%, who undergo CCTA, and in whom CCTA will identify presence of at least 1 significant coronary plaque (producing a luminal narrowing of at least 50%).Ability to provide informed consent.Age over 18 years.

Exclusion criteria:

Patients with pre-test probability of CAD >85% or <15%.Electrocardiographic evidence of ST-segment elevation acute myocardial infarction.Presence of pre-existing CAD including prior myocardial infarction.History of coronary artery revascularization (by percutaneous coronary intervention, stent, or bypass graft surgery).Atrial fibrillation or other irregular rhythm.Unwillingness or incapacity to provide informed consent.Allergy to iodine contrast media.Inability to tolerate beta-blocker medication.Renal insufficiency (serum creatinine values higher than 1.5 mg/dL) or renal failure requiring dialysis.Pregnant women or lactation.Active malignancy or malignancy within the last 5 years prior to enrolment.Conditions associated with an estimated life expectancy of under 2 years.Coronary calcium score >1000.

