### Outcomes

2.8

The primary outcome of the study is represented by the rate of MACE during follow-up. Secondary outcome refers to coronary plaque vulnerability associated to plaque eccentricity, based on the number of vulnerability markers in eccentric versus concentric plaques.

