### Participation timeline

2.9

Screening (Day 0)

Obtain and document consent from participant on study consent form.Verify inclusion/exclusion criteria.Imaging: 128-multislice CT angiography scanning and basic plaque assessment—presence of coronary plaque and degree of luminal narrowing.

Baseline (day 0):

-Obtain demographic information, medical history, medication history, alcohol, and tobacco use history.-Record results of physical examinations and 12-lead ECG.-Collect blood specimens.-Imaging: image post-processing for complex plaque assessment—plaque morphology, composition, and geometry

Visit 1 (month 6):

-Record results of physical examinations, 12-lead ECG, and medical history.-MACE assessment.

Visit 2 (month 12):

-Record results of physical examinations, 12-lead ECG, and medical history.-MACE assessment.

Visit 3 (month 18):

-Record results of physical examinations, 12-lead ECG, and medical history.-MACE assessment.

Final study visit (month 24):

-Record results of physical examinations, 12-lead ECG, and medical history.-Repeat CCTA and plaque assessment.-End-point evaluation.

Figure 1 illustrates the GEOMETRY diagram with the flowchart that will be used in the study.

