## Conclusions

4

In conclusion, GEOMETRY will be the first CCTA-based study that will investigate the impact of geometric distribution of coronary atheromatous plaque on the future risk of cardiovascular events and on the rate of plaque progression, introducing and validating a new potential feature of plaque vulnerability represented by plaque geometry.

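### Plaque progression is declared as a study outcome, objective and conclusion, but section 2.8 omits it, and the stated two-group tests use neither baseline plaque volume nor the clustering of lesions within patients

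*Protocol article*

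**What the plan says.** The protocol article names plaque progression in four places.

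- Abstract, Material and methods: "Study outcomes will consist in the rate of major cardiovascular events and the rate of plaque progression during follow-up".
- Section 1.2, secondary objective: to "evaluate the association of plaque eccentricity with plaque vulnerability and plaque progression after 2 years of follow-up".
- Conclusions (section 4, and the abstract's conclusion in the same terms): the study will examine the impact of plaque geometry "on the future risk of cardiovascular events and on the rate of plaque progression".
- Section 2.9, final visit at month 24, which supplies the data: "Repeat CCTA and plaque assessment".

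Section 2.8 gives a different list. On the primary outcome: "The primary outcome of the study is represented by the rate of MACE during follow-up". Its next sentence reads: "Secondary outcome refers to coronary plaque vulnerability associated to plaque eccentricity, based on the number of vulnerability markers in eccentric versus concentric plaques". Progression does not appear there.

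Section 2.6.2 has plaque volume measured for each lesion. Section 2.11 names the t test, the Mann–Whitney U test and the Fisher exact test, and no adjustment. Section 2.1 describes a non-randomised cohort. Section 2.5 forms the groups by patient, while the secondary outcome in 2.8 compares plaques. In 1.2, MACE is defined as "all-cause mortality, cardiovascular death, myocardial infarction, repeated revascularization, repeated hospitalizations for cardiovascular related incidents, cerebrovascular events".

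**The concern.** The section that defines the outcomes disagrees with the abstract, the objective and the conclusions. The mismatch runs both ways: progression is missing from 2.8, and the marker count in 2.8 is not one of the abstract's two outcomes. The article does not define progression by metric, threshold or unit of analysis (patient or lesion). A conclusion about its rate would then rest on an outcome that could be settled after the month-24 scans are read.

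Two analysis questions follow if progression stays. First, the stated tests use neither the baseline volume nor the fact that one patient may contribute several lesions. Second, some lesions will have no usable month-24 measurement because the patient died or the lesion was revascularised. Both are MACE components, and MACE is the outcome on which the groups are expected to differ.

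**Working it through.** **1. The sections side by side**

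| Place | MACE | Plaque progression | Vulnerability markers |
|---|---|---|---|
| Abstract, study outcomes | yes | yes | no |
| 1.2 Objectives | yes (primary) | yes (secondary) | yes (secondary) |
| 2.8 Outcomes | yes (primary) | **no** | yes (secondary) |
| Conclusions | yes | yes | plaque geometry named as a vulnerability feature |

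Only 2.8 leaves progression out where MACE is named.

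**2. The plan's own figure**

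Section 2.10 gives 500 per group, 90% power, event-free 0.90 against 0.954, two-sided alpha 0.05. The pooled-variance formula is n = [1.960·√(2·p̄·q̄) + 1.282·√(p1q1 + p2q2)]² / d², with p̄ = 0.927 and d = 0.054:

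- 1.960·√0.1353 + 1.282·√0.1339 = 0.721 + 0.469 = 1.190
- 1.190² / 0.054² ≈ 486 per group; power with 500 is 0.908

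The figure reproduces. It covers MACE only; nothing is sized for progression.

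**3. Baseline adjustment**

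Let r be the correlation between baseline and month-24 volume. With equal variances at both times and groups balanced at baseline, residual variance is proportional to 1 − r² for the adjusted analysis and 2(1 − r) for the raw change. The ratio is (1 + r)/2:

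- r = 0.5: 0.75, so 25% less variance
- r = 0.8: 0.90, so 10% less variance

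The article does not give r; these values are assumptions. In a non-randomised cohort the groups may differ at baseline. The adjusted and raw analyses then answer different questions, which is why both should be shown.

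**4. Loss from the repeat scan: proportions**

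The article gives no progression rate and no loss rate, so everything here is assumed. Take true progression of 30% (eccentric) and 20% (non-eccentric). Observed rate = progressors kept / (progressors kept + non-progressors kept).

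| Assumed loss, eccentric vs non-eccentric | Eccentric | Non-eccentric | Difference |
|---|---|---|---|
| Progressors 50% vs 25%, non-progressors none | 0.15/0.85 = 17.6% | 0.15/0.95 = 15.8% | about 2 points |
| Progressors 50% vs 25%, non-progressors 20% vs 10% | 0.15/0.71 = 21.1% | 0.15/0.87 = 17.2% | about 4 points |
| Progressors 50% vs 25%, non-progressors 40% vs 20% | 0.15/0.57 = 26.3% | 0.15/0.79 = 19.0% | about 7 points |
| Event rates of 2.10 (10% vs 4.6%), all losses falling on progressors | 0.20/0.90 = 22.2% | 0.154/0.954 = 16.1% | about 6 points |
| First row reversed: progressors 25% vs 50%, non-progressors none | 0.225/0.925 = 24.3% | 0.10/0.90 = 11.1% | about 13 points |

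The fourth row assumes that the higher event rate belongs to the eccentric group and that every event prevents rescanning. The last row shows that the difference can also widen.

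**5. Loss from the repeat scan: continuous change**

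Simulation with progression SD 1, loss more likely for faster-progressing lesions (logistic slope 0.5 to 1.0 per SD), and a true difference of 0.30 SD:

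| Unassessable, non-eccentric vs eccentric | Observed difference (SD) |
|---|---|
| 4.6% vs 10% | 0.25 to 0.27 |
| 20% vs 30% | 0.22 to 0.25 |
| 30% vs 50% | 0.13 to 0.21 |
| 40% vs 40% | about 0.30 |

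With no true difference, the unequal-loss patterns give a spurious difference of about −0.02 to −0.16 SD. The effect is negligible under equal loss, small at the event rates of 2.10, and material only under heavy unequal loss.

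**The case against.** The strongest reply is that an article condenses a fuller plan. Adjustment, clustering and the handling of unassessable lesions belong in an analysis plan that is not shown. That stands for the modelling detail, whose absence alone is not an error. It does not cover the contradiction: an Outcomes section was written, and it disagrees with three other parts of the same article.

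A second reply is that the baseline-adjusted model is a preference. Section 2.11 is generic and never says that progression will be a raw change; a rate could be a proportion compared by the Fisher exact test. The variance gain also depends on balance that this design does not provide. This stands in part. Adjustment is an improvement rather than a correction, and it should not replace the unadjusted result.

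Three stronger readings are tempting, and the article does not support them.

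- **Progression would be compared only in event-free, unstented lesions.** Section 2.9 lists the repeat scan without restriction. Survivors of infarction, stroke or a cardiovascular admission could be rescanned. Revascularisation is a MACE component, but treatment of study lesions after baseline is not described.
- **The result is bound to be biased toward no difference because eccentric lesions are lost faster.** Section 1.1 says that ruptured plaques are usually eccentric, which is not the rupture rate among eccentric plaques. The Discussion links eccentricity to low FFR, but nothing links low FFR to loss from the scan.
- **The month-24 scan serves no listed outcome.** The marker count in 2.8 has no time point, so the second scan could serve it.

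**Conclusion.** The inconsistency holds on the face of the article and needs no assumption: progression is an outcome in the abstract, an objective in 1.2 and a claim in the conclusions, but not an outcome in 2.8. The stated tests are also a weak basis for it, since they ignore a baseline measurement already planned and the grouping of lesions within patients.

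Differential loss is a risk to plan for, not a demonstrated bias. Deaths and revascularised lesions will leave gaps, but how many, in which group and in which direction cannot be derived from the document. A reader might cite the shrinkage from 10 points to 2 as the expected effect. It is one extreme case, with no loss at all among non-progressors; the other loss patterns with more loss in the eccentric group leave about 4 to 7 points. The primary outcome and its sample size are unaffected. This is worth correcting at secondary-outcome level.

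**What to change.** Reconcile the abstract, 1.2, 2.8, 2.9 and the conclusions in one of two ways.

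**Keep progression.** List it in 2.8 as a secondary outcome: change in plaque volume of each significant baseline lesion from day 0 to month 24. In 2.11:

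- Analyse month-24 volume adjusted for baseline volume, with patient as cluster. Report the unadjusted change alongside, because the groups are not randomised.
- Report the number of unassessable lesions, with reasons, by group.
- Add a sensitivity analysis on a binary progression outcome, with its threshold fixed before the month-24 scans are read. Count lesions with culprit infarction or any post-baseline revascularisation as progressed.

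**Or remove it** from the abstract, objective and conclusions, and state what the month-24 plaque assessment is for.

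The cost is wording in 2.8 and 2.11 and a little more analysis. The volumes are already planned; the sensitivity analysis also needs event dates and the identity of the affected lesion. It overlaps with MACE, and revascularisation need not reflect progression, so it should be labelled as supportive.

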**Conclusion::**

In conclusion, GEOMETRY will be the first CCTA-based study that will investigate the impact of geometric distribution of coronary atheromatous plaque on the future risk of cardiovascular events and on the rate of plaque progression, introducing and validating a new potential feature of plaque vulnerability represented by plaque geometry.

## Introduction

1

### Background and rationale

1.1

Ischemic heart disease represents the leading cause of mortality worldwide, causing 9.4 million of deaths in 2016.^[1]^ Atherosclerosis represents the underlying condition leading to myocardial ischemia, ultimately resulting in acute coronary syndromes (ACS) and having devastating consequences on public health. The vast majority of ACSs are the consequence of a sudden modification in coronary plaque morphology leading to plaque rupture or erosion, the 2 principal mechanisms triggering an acute coronary event.^[2]^ Atheromatous plaques that are prone to rupture or erosion following a complex process of transformation and alteration of plaque composition are known as vulnerable coronary plaques and can be easily identified nowadays with the help of modern imaging techniques.^[3,4]^ Due to the recent progress in the field of coronary computed tomography angiography (CCTA), it has emerged as a valuable noninvasive imaging tool for assessing atheromatous plaque morphology and composition. Moreover, CCTA-based imaging-derived markers associated with vulnerability have been validated as reliable indicators of the plaque-associated risk. Such key CCTA features of plaque vulnerability identified by previous studies include positive remodeling (PR), low-attenuation plaque (LAP), napkin-ring sign (NRS), and spotty calcifications (SC).^[5,6]^ Interestingly, intravascular ultrasound studies demonstrated that ruptured coronary plaques are usually eccentric.^[7]^ A combined intravascular ultrasound (IVUS) and optical coherence tomography (OCT)-based study reported that lesions demonstrating plaque erosion had a greater plaque eccentricity index than those with plaque rupture or calcified nodules (*P* < .001 and *P* < .001).^[8]^ At the same time, progression of atherosclerotic lesions was more frequent in eccentric lesions than in concentric ones.^[7,9]^ However, the role of lesion eccentricity as a CCTA feature of plaque vulnerability has not been investigated so far. Furthermore, the impact of lesion geometry, as defined by the type of eccentricity (transversal or longitudinal), on the degree of vulnerability is unclear.

Here we present the study protocol of the GEOMETRY trial, a prospective, single center, cohort study in which we aim to investigate the relationship between plaque geometry (as expressed by cross-sectional and longitudinal plaque eccentricity), on one hand, and the risk for major adverse cardiac events (MACE) during 2 years of follow-up, in order to validate plaque eccentricity as a new CCTA marker of coronary plaque vulnerability.

### Study objectives

1.2

The primary objective of the study is to evaluate the association between different patterns of plaque geometry and the risk for major adverse cardiac events MACE (defined as all-cause mortality, cardiovascular death, myocardial infarction, repeated revascularization, repeated hospitalizations for cardiovascular related incidents, cerebrovascular events) during a 2-year follow-up.

The secondary objective of the study is to evaluate the association of plaque eccentricity with plaque vulnerability and plaque progression after 2 years of follow-up.

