### Study procedures and outcome assessment

2.6

In all patients clinical data including sex, age, comorbidities, history of coronary artery disease, stroke, peripheral arterial disease, diabetes, smoking status, as well as clinical status and laboratory tests (creatinine, total cholesterol, low-density lipoprotein [LDL]-cholesterol, triglycerides) will be recorded. All patients will undergo CCTA scanning of the coronary arteries at screening and will be enrolled in the study if CCTA reveals the presence of at least 1 obstructive coronary plaque in any coronary artery. In randomized patients, CCTA scanning will be followed by complex image postprocessing for assessment of plaque composition, morphology, and geometry, using available research software for plaque reconstruction and analysis.

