Various recent studies reported the role of CT-derived features for characterization of the functional significance of a coronary plaque.^[23,24]^ A recent study published by Kang et al^[15]^ demonstrated that coronary lesion geometry has a direct impact on the functional significance of a coronary stenosis, showing that complex coronary lesions are independently associated with reduced fractional flow reserve (FFR) values and that lesion eccentricity is the most significant independent predictor for low FFR. In the GEOMETRY study presented here, we extended this hypothesis to investigate for the first time the impact of lesion geometry on plaque vulnerability and the association between geometric distribution of atheromatous plaques and the related risk of future cardiovascular events.

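### The primary endpoint counts only repeated revascularisation, although prior revascularisation is excluded and no index procedure is defined, so a first procedure during follow-up is not an event as written

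*Protocol article*

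**What the plan says.** Section 2.8 (Outcomes) states: "The primary outcome of the study is represented by the rate of MACE during follow-up". It does not define the components. The only definition is in section 1.2 (Study objectives), where MACE is "defined as all-cause mortality, cardiovascular death, myocardial infarction", followed by "repeated revascularization, repeated hospitalizations for cardiovascular related incidents, cerebrovascular events".

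Section 2.3 (Study population) lists as exclusions "Presence of pre-existing CAD including prior myocardial infarction" and "History of coronary artery revascularization (by percutaneous coronary intervention, stent, or bypass graft surgery"). The same section requires at least one plaque with 50% or more luminal narrowing. Section 2.6 repeats this as an enrolment condition: "CCTA reveals the presence of at least 1 obstructive coronary plaque in any coronary artery".

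Section 2.9 (Participation timeline) goes from screening and baseline on day 0 to visits at months 6, 12, 18 and 24. It mentions no index revascularisation or index admission. Section 2.10 (Sample size) assumes that 90% are event-free and does not say which reading of the components this covers.

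**The concern.** A repeated procedure needs an earlier one. The exclusions remove every patient who had one before enrolment, and the article describes none at enrolment. Two readings of the stated wording remain, and neither suits a study of plaque risk:

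- **Literal.** A first revascularisation during follow-up is not an event. Nor is a first cardiovascular admission.
- **Repeat after treatment prompted by the screening scan.** Only patients revascularised after that scan can have the component, so early treatment decides who is at risk of it.

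An analyst might instead drop the word and count any revascularisation. Every patient enters with an obstructive plaque, so procedures prompted by the qualifying finding would become MACE unless a rule sets them aside. They could plausibly differ between the groups, since the Discussion cites a study in which "lesion eccentricity is the most significant independent predictor for low FFR".

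At stake are which events make up the primary result, and whether the assumed 10% event rate refers to the same events.

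**Working it through.** **1. The text side by side**

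| Element | Where | Content |
|---|---|---|
| Revascularisation component | 1.2 | repeated only |
| Hospitalisation component | 1.2 | repeated only |
| Prior revascularisation, known CAD, prior MI | 2.3 | excluded |
| Prior cardiovascular admission | 2.3 | not excluded |
| Index procedure or admission | 2.6, 2.9 | none described |
| Rule for procedures prompted by the screening CCTA | whole article | none stated |

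The conflict with eligibility concerns revascularisation. For hospitalisation, section 2.6 records history of stroke and peripheral arterial disease, so an enrolled patient may have been admitted before. That wording is loose but not contradicted.

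**2. The plan's own figure**

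Inputs from section 2.10: n = 500 per group, 90% event-free, a difference of 0.054, two-sided alpha 0.05, stated power 90%. The event rates are therefore p1 = 0.10 and p2 = 0.046.

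Power = Φ[(|p1 − p2| − 1.96·SE0)/SE1], where SE0 = √[2·p̄(1 − p̄)/n] and SE1 = √[(p1(1 − p1) + p2(1 − p2))/n].

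- p̄ = 0.073
- SE0 = √(2 × 0.073 × 0.927/500) = 0.01645
- SE1 = √((0.0900 + 0.0439)/500) = 0.01636
- Power = Φ[(0.054 − 0.0322)/0.01636] = Φ(1.33) = 0.908

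The stated 90% reproduces; 90% power needs 486 per group by the same method. A change in the other direction (90% to 84.6% event-free) gives only about 73%, so 95.4% is the reading that matches the stated power. Expected events: 500 × 0.10 + 500 × 0.046 = 50 + 23 = 73.

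**3. Illustration: first events left uncounted**

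Assume that a share f of the 73 events are first revascularisations or first admissions that the wording does not count, with the same share in both groups. The rates become 0.10(1 − f) and 0.046(1 − f).

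| f (assumed) | Rates | Events left | Power |
|---|---|---|---|
| 0 | 10.0% vs 4.6% | 73 | 91% |
| 20% | 8.0% vs 3.68% | about 58 | 83% |
| 40% | 6.0% vs 2.76% | about 44 | 71% |
| 60% | 4.0% vs 1.84% | about 29 | 53% |

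**4. Illustration: deleting the word with no further rule**

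Assume that a share r of patients has a procedure prompted by the screening scan, equally in both groups and independently of later events. Each rate becomes 1 − (1 − p)(1 − r).

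- r = 10%: 1 − 0.90 × 0.90 = 19.0% vs 1 − 0.954 × 0.90 = 14.1%; power 54%.
- r = 20%: 1 − 0.90 × 0.80 = 28.0% vs 1 − 0.954 × 0.80 = 23.7%; power 34%.

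The article gives neither f nor r. Both ranges are assumptions.

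**The case against.** The best defence is that *repeated* is habitual wording in MACE definitions. It may mean any procedure after treatment prompted by the scan, in which case index procedures are already left out. Blanking windows and planned/unplanned flags are commonly left to a fuller protocol or analysis plan, so their absence alone would be no finding. Death, myocardial infarction and cerebrovascular events still count at first occurrence, and an urgent first revascularisation for infarction is captured through the infarction.

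Much of this stands. It limits the loss to revascularisations and admissions without another counted event. It does not remove the conflict, because the stated wording presupposes an earlier procedure that the eligibility criteria rule out and the article never introduces. On the charitable reading, the component still applies only to treated patients.

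Three stronger readings are tempting but unsupported:

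- **A death could count twice**, because cardiovascular death is listed beside all-cause mortality. Section 2.10 works with event-free proportions and section 2.11 compares categorical variables by the Fisher exact test, so each patient is either event-free or not. The listing is redundant but harmless to that comparison.
- **The endpoint is biased towards the hypothesis by scan-driven procedures.** This arises only if *repeated* is ignored. The article gives no index procedure rate in either group and describes no FFR testing or revascularisation pathway. A difference between groups is plausible, not documented. With equal shares the effect is dilution.
- **The eligibility criteria contradict *repeated hospitalizations* too.** No exclusion concerns earlier cardiovascular admission.

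**Conclusion.** The concern holds for the revascularisation component: the stated definition conflicts with the eligibility criteria, and on the wording as it stands a first revascularisation during follow-up is not a primary event. The hospitalisation component shares the literal gap but not the contradiction.

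The sample size arithmetic is sound. What cannot be established is which events its 10% rate covers. The fall in power to about 83%, 71% or 53% assumes that 20%, 40% or 60% of the 73 expected events go uncounted, equally in both groups. These figures show sensitivity and do not estimate the loss in this trial. A reader might infer that the endpoint fails altogether; the remaining components, which count from the first event, do not support that.

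**What to change.** In section 1.2, replace the two components with first unplanned coronary revascularisation and first unplanned cardiovascular hospitalisation after the screening CCTA. State that procedures planned on the basis of that CCTA are not events; record each with its date and a planned/unplanned flag, and examine them in a sensitivity analysis. In section 2.10, state that the 90% event-free assumption refers to this definition, or revise it. Cardiovascular death may be shown as a subset of all-cause death for tidiness; the planned comparison does not depend on it.

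The cost is a wording change plus one dated field on the event form. The downside is fewer soft events than under a definition that counts any revascularisation.
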